## Abstract

**Background:**

According to the World Health Organization (WHO), dental caries is considered one of the greatest pediatric health problems in the world, due to its high prevalence and incidence. Therefore, the early diagnosis of caries lesions is a fundamental procedure for planning treatment aimed at prevention, minimal intervention and promotion of oral health. The present study aims to evaluate, through a randomized and controlled clinical study, which is the best strategy for diagnosing primary caries lesions located in the interproximal region.

**Materials and methods:**

Eighty patients, aged between 4 and 10 years will be randomized and allocated into 2 groups for analysis and comparison of methods for diagnosing caries lesions. The following diagnostic methods will be analyzed and compared: visual clinical examination using ICDAS (International Caries Detection and Assessment System), the iTero Element 5D System (intraoral scanner with near infrared imaging (NIRI) technology) and bitewing radiography (BWX). All evaluations will be carried out by 02 examiners. Examiners will be trained and calibrated to use the visual and radiographic criteria and also to use the iTero 5D intraoral scanner, following the manufacturer’s instructions.

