## Materials and methods

A randomized, controlled, clinical trial will be conducted. After receiving clarifications regarding the objectives and procedures of the study, the guardians of the children will agree to participate by signing a statement of informed consent.

Eighty individuals who meet the inclusion criteria will be divided into 02 groups (n = 40). For the random distribution of volunteers, randomization will be performed by drawing lots, using the research randomizer program (https://www.randomizer.org/). Group 1: Visual Inspection + BWX Radiographic Assessment + Assessment of the iTero Element 5D scan and Group 2: Visual Inspection + Assessment of the iTero Element 5D scan + BWX Radiographic Evaluation. For each group, the investigator will assess and document the findings of each diagnostic test before moving on to the next test.

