### Visual inspection

The examiners will evaluate the surfaces included in the study independently and without knowledge of the results of the other examiner, after prophylaxis, using a mouth mirror and a WHO probe or "Ball point". The evaluations will be carried out in a dental chair with the aid of a reflector. The teeth will be examined while moist, and afterwards, they will be dried for 5 seconds with the use of a triple syringe.

For visual inspection, the International Caries Detection and Assessment System (ICDAS) evaluation system will be used. The ICDAS criteria are described in Fig 2.

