### Clinical protocol

The attendance of volunteers will follow the following phases:
Anamnesis and Clinical Examination;Verification of eligibility criteria (inclusion and exclusion criteria);Talk with those responsible to inform if the volunteer fits or not the research inclusion criteria. If the volunteer does not fit, he/she/they will be referred to the discipline of Pediatric Dentistry at *Universidade Metropolitana de Santos*;Signature of the Informed Consent Form by the guardians of patients who meet the inclusion criteria. Application form;Visual Inspection (ICDAS);Intraoral Scan: volunteers will be scanned intraorally (iTero Element 5D System). The order of iTero 5D and BWX assessment will be performed according to the study Groups (1 or 2);Radiographic Evaluation: BWX Radiographs;Caries Assessment Form.

The study ends when the volunteers complete all phases of the protocol and follow-up, if necessary. Clinical evaluation and subsequent treatment, if indicated, will be performed upon completion of the study.

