### Organization and statistical treatment of data

Non-parametric McNemar’s Chi-Square test will be used for paired nominal data. This test enables the comparison of the detection proportions between the two methods. Kappa coefficients will be calculated to assess the agreement between the two methods.

Differences in detecting the existence of primary interproximal caries lesions above the gingiva (sensitivity and specificity) between the iTero Element 5D system and BWX and the corresponding 90% confidence interval for the differences will be calculated. A minimum of 154 surfaces will ensure a power of 0.8, with an alpha = 0.05. Moderate agreement (Kappa≥0.5) is expected between iTero Element 5D system and radiography. Non-inferiority of the iTero Element 5D is expected as compared with radiography and evaluated by the McNemar’s Chi-Square test.

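### Test order is the only randomised factor, but the stated analysis ignores it, so unequal carry-over between BWX and iTero could shift the difference unseen

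*Protocol article*

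**What the plan says.** The Abstract of the protocol article says that the children "will be randomized and allocated into 2 groups for analysis and comparison of methods for diagnosing caries lesions". Materials and methods shows how the groups differ. "Group 1: Visual Inspection + BWX Radiographic Assessment + Assessment of the iTero Element 5D scan"; "Group 2: Visual Inspection + Assessment of the iTero Element 5D scan + BWX Radiographic Evaluation". The Clinical protocol section confirms that the group sets the order of the two imaging tests. Forty children go to each group.

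Reading is sequential: "the investigator will assess and document the findings of each diagnostic test before moving on to the next test". The only masking stated is under Visual inspection, where the examiners work "independently and without knowledge of the results of the other examiner". No masking of one test's result from the reading of the next is stated.

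The analysis section gives McNemar's test for paired data: "This test enables the comparison of the detection proportions between the two methods". It adds kappa, 90% intervals for the iTero versus BWX differences, and a non-inferiority assessment by McNemar's test. It does not mention group, sequence or order. Sample calculation gives a 5% margin and a single total of 149 surfaces from 80 patients.

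**The concern.** Every child has both imaging tests, so the randomised groups are two orders of the same tests. The second image is read after the first has been documented, and reading it may be influenced by what was already found. If that influence differs between the two tests, the iTero minus BWX difference moves even when the groups are perfectly balanced.

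The design collects what is needed to look at this, but the analysis it names has no place for it. At stake is a non-inferiority conclusion against a 5-point margin, together with a kappa that mixes two reading orders.

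**Working it through.** **1. The plan's own figure.** The article's one-sided formula is n = [z_α√S + z_β√(S − D²)]² / D², with S = p01 + p10 + M and D = p10 + M − p01. Inputs from Sample calculation are p01 = 0.0006, p10 = 0.001, M = 0.05, α = 0.05 one-sided and power 0.8. Then S = 0.0516, D = 0.0504 and n = 123.5, so 124. Adding 20% gives 124 × 1.2 = 148.8, so 149 (124 + 25). The stated total reproduces. (The printed base of 12, and the 154 in the analysis section, are separate matters.) One paired comparison is sized, and no input concerns order.

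**2. Effect of order on the pooled difference.** Let d be the true iTero minus BWX difference, a the gain in detection when iTero is read second, b the gain when BWX is read second, and w1, w2 the groups' shares of surfaces.
- Group 1 difference: d + a
- Group 2 difference: d − b
- Pooled: d + w1·a − w2·b; if a = b = e, this is d + e(w1 − w2)

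Shift in points from d (all values of a, b and the splits are assumptions):

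| a | b | 50:50 | 55:45 | 60:40 |
|---|---|---|---|---|
| 5 | 5 | 0 | 0.5 | 1.0 |
| 10 | 10 | 0 | 1.0 | 2.0 |
| 10 | 5 | 2.5 | 3.25 | 4.0 |
| 10 | 0 | 5.0 | 5.5 | 6.0 |
| 0 | 10 | −5.0 | −4.5 | −4.0 |

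**3. How far surfaces may be out of balance.** Children are split 40:40, but surfaces per child vary. With between-child SD s (not in the documents), the SD of w1 − w2 is about √80 × s / 149 = 0.06s. A 60:40 split means w1 − w2 = 0.20, which is 3.3 SDs at s = 1 and 1.7 SDs at s = 2. A one-SD imbalance at s = 1 with e = 10 shifts the result by 0.6 points.

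**4. What order stratification does.** The equal-weight average is ½[(d + a) + (d − b)] = d + (a − b)/2. With a = b it returns d whatever the surface split. With a = 10 and b = 0 it still gives d + 5.

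The contrast between the two group differences is a + b. It is 10 points both for 10/0 and for 5/5, so it signals an order effect but not whether the effect is unequal. Separating the two needs each test's detection proportion by group: iTero in Group 1 minus iTero in Group 2 estimates a, and BWX in Group 2 minus BWX in Group 1 estimates b.

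**5. Precision, ignoring clustering.** Assume discordant proportions of 0.06 and 0.10 (the article prints these digits as percentages, at which only 149 × 0.0016 = 0.24 discordant surfaces are expected). The pooled SE is √[(0.16 − 0.04²)/149] = 0.033. The SE of the between-order contrast is twice that, 0.065. The contrast detectable at 80% power, two-sided 5%, is about 18 points.

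For the comparison of first imaging tests, take about 74.5 surfaces per group and an assumed detection rate of 10% to 30%. The 90% half-width is 1.645 × √[2p(1 − p)/74.5], or 8.1 to 12.4 points.

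**The case against.** The strongest reply is that randomising order is itself the safeguard. A common second-read effect cancels in expectation at 1:1, with or without an order term, and what remains is chance imbalance in surface counts. That stands. A reader might infer that the randomisation serves no purpose unless order is analysed, or that the pooled estimate is systematically biased. The documents support neither. The 2-point shift needs both a large assumed effect and an unlikely split.

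A second reply is that the article never says in words that the groups are pooled, and that a fuller analysis plan could add results by order. Pooling is indeed an inference, from a single surface total and a comparison of two methods with no mention of group. But the article goes beyond silence: it fixes McNemar's test for non-inferiority, and the plain test cannot carry order.

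A third reply is that order adjustment does not cure the case that matters most. That stands too (step 4). Nor would an order term reveal equal anchoring, where second reads drift towards first reads alike in both orders, pulling the difference towards zero and raising kappa. In a simulation at a true deficit equal to the margin (assumed discordant rates 0.105 and 0.055, 149 independent surfaces), copying in 25% or 50% of discordant pairs raised the chance of declaring non-inferiority from about 6% to 13% or 32%. Only masked reading would deal with that.

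**Conclusion.** The point holds in a limited form. The trial randomises order and nothing else, and its stated analysis makes no use of order. For a common second-read effect the cost is small: no shift at equal surface counts, and 1 point at 55:45 under an assumed 10-point effect. For unequal carry-over the shift can reach the whole 5-point margin (assumed 10 and 0) at perfect balance, with nothing in the planned output to reveal it.

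These sizes rest on assumed effects. The documents give no estimate of any order effect, so it cannot be said that the result will be biased, only that such a bias would go unseen.

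**What to change.** Keep the paired comparison and stratify it by randomised order:
- Estimate the iTero minus BWX difference within each group and average the two with equal weight, with variance clustered by child. This can be a Mainland-Gart type analysis, or a GEE with method, position and group; an identity link keeps the estimate on the scale of the margin.
- Report the difference, kappa and each test's detection proportion separately for Group 1 and Group 2, as estimates with intervals rather than relying on a significance test for order.
- Add BWX in Group 1 versus iTero in Group 2 (first imaging test only) as a descriptive sensitivity analysis. It is too imprecise to judge a 5-point margin, and visual inspection still precedes both tests.

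State the limits alongside: adjustment corrects for unequal surface counts but not for unequal carry-over or equal anchoring; reporting by group can at best make unequal carry-over visible; and power for an order contrast is low.

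The cost is mainly wording, since order is known from allocation and no extra children or data are needed. It does replace the plain McNemar test on which the sample size rests. The loss from equal weighting is small: with equal variance per surface, the variance rises by a factor 1/(4·w1·w2), which is 1.01 at 55:45 and 1.04 at 60:40.

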**Trial registration:**

NCT04900246 in ClinicalTrial.gov. First released in 05/11/2021 and last updated in 10/06/2021.

## Introduction

Currently, dental caries is defined as a chronic and infectious disease of multifactorial etiology with a higher incidence in school-age children. According to the World Health Organization (WHO), it is considered one of the greatest pediatric health problems in the world, due to its high prevalence and significant incidence [1, 2].

For years, the main methods used in the dental clinic for diagnosing and evaluating the extent of caries lesions were: visual, tactile and radiographic clinical examination, classified as traditional or conventional detection methods [3]. For radiographic caries detection, the recommended technique is the bitewing (BWX), also called interproximal. When properly performed, it is capable of providing important information to complement the diagnosis, as interproximal radiography allows a better estimate of the more sensitive depth of proximal and occlusal caries in dentin than clinical inspection alone. Furthermore, monitoring of caries lesions can be more reliable and accurate than conventional clinical examination. However, it must be remembered that radiographic images tend to underestimate the real extent of demineralized areas [4–6].

The subjectivity of the visual clinical examination for the diagnosis of caries lesions is a great concern, so, to standardize the diagnoses, indexes can be used as a tool. ICDAS is an acronym for International Caries Detection and Assessment System, that is, an international system for the detection and assessment of caries lesions. This system seeks to standardize the detection of caries lesions and this index can be used for clinical practice, research, teaching and epidemiology [7].

Interproximal radiography helps to identify hard tissue demineralization [8], but a single radiography cannot determine whether demineralization is a sign of active or inactive caries lesions, nor is it able to distinguish between cavitated lesions and lesions with an intact surface [9].

Currently, new technologies have been developed and validated in order to complement and even surpass other methods, such as the Low-Frequency Fluorescent Laser (DIAGNOdent device—Kavo, Germany), the measurement of electrical resistance offered by the dental element (ECM device—LODE, Netherlands), the DIFOTI device, Quantitative Light-Induced Fluorescence (QLF) and Computed Tomography [10, 11].

Near Infrared Imaging (NIRI) technology is a non-ionizing imaging technology that leverages differences in infrared light scattering and absorption depending on the degree of mineralization of the tooth. *In vitro* and *in vivo* studies using NIRI technology for diagnosing caries lesions have yielded encouraging results [12]. Commercially available systems already use this technology to provide grayscale images for diagnosing caries lesions in enamel and dentin [13].

Early diagnosis of caries lesions is a fundamental procedure for planning treatment aimed at prevention, minimal intervention and promotion of oral health. Therefore, this study aims to verify the best strategy for diagnosing caries lesions among visual clinical examination through ICDAS, the iTero Element 5D System (intraoral scanner with NIRI technology) and bitewing radiography (BWX).

## Materials and methods

A randomized, controlled, clinical trial will be conducted. After receiving clarifications regarding the objectives and procedures of the study, the guardians of the children will agree to participate by signing a statement of informed consent.

Eighty individuals who meet the inclusion criteria will be divided into 02 groups (n = 40). For the random distribution of volunteers, randomization will be performed by drawing lots, using the research randomizer program (https://www.randomizer.org/). Group 1: Visual Inspection + BWX Radiographic Assessment + Assessment of the iTero Element 5D scan and Group 2: Visual Inspection + Assessment of the iTero Element 5D scan + BWX Radiographic Evaluation. For each group, the investigator will assess and document the findings of each diagnostic test before moving on to the next test.

### Inclusion criteria

Patients of any sex who seek dental treatment at the Dentistry Clinic of *Universidade Metropolitana de Santos*.Be between 04 and 10 years old;Good general health;Present at least two tooth surfaces that can be included in the study.

### Exclusion criteria

Dental surfaces with proximal restorations;Surfaces with evident proximal cavities (marginal crest break);Absence of adjacent tooth (absence of proximal contact).

### Ethics and dissemination

This study has been approved by the Ethics Committee of *Universidade Metropolitana de Santos* (UNIMES) under process number 4.742.686 and will be conducted in accordance with the norms governing research involving human subjects stipulated in Resolution 466/2012 of the Brazilian National Board of Health. Changes in the protocol will be reported to this same committee.

### Ethics statement

Individuals deemed eligible will receive clarifications regarding the objectives and procedures of the study and those who agree to participate will sign a statement of informed consent. The identity of all individuals will be preserved throughout all stages of the research. No harms are expected.

### Procedures

This protocol is in accordance with the 2013 Standard Protocol Items: Recommendations for Interventional Trials (SPIRIT) Statement (Fig 1) and the SPIRIT checklist can be found as S1 File.

**Fig 1 pone.0273104.g001:**
[figure not shown]
SPIRIT figure as recommended by 2013 SPIRIT statement.

### Methods used to diagnose caries lesions

All evaluations will be carried out by 02 examiners. Examiners will be trained and calibrated to use the visual and radiographic criteria and also to use the iTero 5D intraoral scanner, following the manufacturer’s instructions. At the stage of evaluation, according to the different diagnostic strategies tested, the participants will initially receive prophylaxis on their teeth with pumice stone, water and a Robinson brush. On the proximal surfaces, hygiene will be completed with dental floss.

### Visual inspection

The examiners will evaluate the surfaces included in the study independently and without knowledge of the results of the other examiner, after prophylaxis, using a mouth mirror and a WHO probe or "Ball point". The evaluations will be carried out in a dental chair with the aid of a reflector. The teeth will be examined while moist, and afterwards, they will be dried for 5 seconds with the use of a triple syringe.

For visual inspection, the International Caries Detection and Assessment System (ICDAS) evaluation system will be used. The ICDAS criteria are described in Fig 2.

**Fig 2 pone.0273104.g002:**
[figure not shown]
Description of the ICDAS criteria for proximal and occlusal surfaces [14].

### BWX radiographic assessment

Participants will be radiographed with a digital X-ray device (DIOX-602, Micro Imagem, Indaiatuba, Brazil) with a regulation of 60 kV and 2 mA and exposure time of 0.10s. The technique used will be the interproximal/bitewing (BWX), with the FIT T1 Digital Sensor (external dimensions: 36.7mm x 24.3mm/sensitive area dimensions: 30.0mm x 20.0mm – 600mm^2^) and the sockets will be standardized with use of Han-Shin radiographic positioners (Jon, São Paulo, Brazil).

### Intra-oral scanning method

For the diagnosis through scanning, the iTero 5D (Align Technology) equipment featuring NIRI technology will be used. This is a diagnostic tool that allows the detection of interproximal and occlusal caries in several stages, from the initial enamel caries to lesions in the amelo-dentin junction, without the use of ionizing radiation. Infrared is the region of the electromagnetic spectrum between 0.7 and 2.0 micrometers (μm). The iTero Element 5D imaging system uses wavelength light (= 850 nm) in an electromagnetic spectrum that, in interaction with the hard tooth tissue, provides additional data on its structure.

### Clinical protocol

The attendance of volunteers will follow the following phases:
Anamnesis and Clinical Examination;Verification of eligibility criteria (inclusion and exclusion criteria);Talk with those responsible to inform if the volunteer fits or not the research inclusion criteria. If the volunteer does not fit, he/she/they will be referred to the discipline of Pediatric Dentistry at *Universidade Metropolitana de Santos*;Signature of the Informed Consent Form by the guardians of patients who meet the inclusion criteria. Application form;Visual Inspection (ICDAS);Intraoral Scan: volunteers will be scanned intraorally (iTero Element 5D System). The order of iTero 5D and BWX assessment will be performed according to the study Groups (1 or 2);Radiographic Evaluation: BWX Radiographs;Caries Assessment Form.

The study ends when the volunteers complete all phases of the protocol and follow-up, if necessary. Clinical evaluation and subsequent treatment, if indicated, will be performed upon completion of the study.

### Sample calculation

Sample size can be calculated from the sample size equation for comparing paired nominal data by using McNemar’s test [15]:

$$n=\frac{{\left[z_{\alpha /2}\sqrt{p_{01}+p_{10}}+z_{\beta }\sqrt{p_{01}+p_{10}-{\left(p_{01}-p_{10}\right)}^{2}}\right]}^{2}}{{\left(p_{10}-p_{01}\right)}^{2}}$$

Similar formulae can be obtained for the one-sided non-inferiority test by substituting *z*_*α*/2_, *p*_10_ with *z*_*α*_ and *p*_10_ + *M*:

$$n=\frac{{\left[z_{\alpha }\sqrt{p_{01}+p_{10}+M}+z_{\beta }\sqrt{p_{01}+p_{10}+M-{\left(p_{01}-p_{10}-M\right)}^{2}}\right]}^{2}}{{\left(p_{10}+M-p_{01}\right)}^{2}}$$

where significance level *α* = 0.05, power 1 –β = 0.8, non-inferiority margin M = 5%, assumed detection rate *p*_01_ = 0.06%, *p*_10_ = 0.1%

The minimum sample size required is 12 surfaces. Assuming the drop off rate to be 20%, an additional 25 surfaces will be recruited. So, the total number of surfaces needed for the clinical trial is 149, requiring 80 patients.

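### The non-inferiority sample-size formula puts the margin into the variance under the alternative, so the stated 80% power is not the power of a test against the 5% margin

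*Protocol article*

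**What the plan says.** The protocol article's Sample calculation section first gives the usual two-sided McNemar sample-size formula for paired proportions. It then moves to non-inferiority: "Similar formulae can be obtained for the one-sided non-inferiority test by substituting" z_alpha for z_alpha/2 and p10 + M for p10. In the displayed result M appears in three places: in the denominator, in the z_alpha square root and in the z_beta square root.

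The inputs are one-sided alpha 0.05, "power 1 –β = 0.8, non-inferiority margin M = 5" (per cent), and "assumed detection rate *p*_01_ = 0.06%, *p*_10_ = 0.1" (per cent). The section then states "The minimum sample size required is 12 surfaces", adds 25 surfaces for a 20% loss and arrives at 149 surfaces in 80 patients.

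The section on organization and statistical treatment of data attaches the power to another number: "A minimum of 154 surfaces will ensure a power of 0.8, with an alpha = 0.05". For the sensitivity and specificity differences between scanner and radiograph it says "the corresponding 90% confidence interval for the differences will be calculated", and it assigns the non-inferiority evaluation to McNemar's chi-square test.

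**The concern.** A non-inferiority margin moves the hypothesis. It is a constant and creates no discordant pairs. Under the assumed truth, the sampling variance of the paired difference depends on p01 and p10 only. A formula that adds M to that variance describes a population with about 5% more discordant surfaces than the plan assumes, so the power it delivers belongs to a different situation.

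Power of 0.8 is the only operating characteristic the article gives. If it does not describe the test against the margin, readers cannot tell what the trial can show. Anyone who later enters more realistic discordance into the same formula will get a wrong requirement, or a wrong power for a given number of surfaces.

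**Working it through.** **Inputs.** From Sample calculation: one-sided alpha 0.05 (z = 1.6449), power 0.8 (z = 0.8416), M = 0.05, p01 = 0.0006, p10 = 0.001. Assumptions: surfaces are independent, and p10 is the proportion positive by the scanner only, as the denominator p10 + M − p01 implies.

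**1. Reproducing the plan's figure.**
- Null term: p01 + p10 + M = 0.0516.
- Shifted difference: d = p10 + M − p01 = 0.0504, so d² = 0.00254.
- Alternative term: 0.0516 − 0.00254 = 0.0491.
- n = [1.6449·√0.0516 + 0.8416·√0.0491]² / 0.00254 = (0.3736 + 0.1864)² / 0.00254 = 123.5, so 124.
- 20% of 124 is 24.8, so 25, and 124 + 25 = 149.

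The formula therefore underlies the stated total. With p01 and p10 exchanged it gives 127.6, which does not lead to 149. The value 124 is an inference, since the text prints 12. The 154 also appears to come from it (123.5/0.8 = 154.4).

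**2. What the formula sizes.** The same n follows from the ordinary one-sided McNemar formula with p10 = 0.001 + 0.05 = 5.1% and p01 = 0.06%. That is a superiority test in a different population.

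**3. The variance under the alternative.** It should be p01 + p10 − (p10 − p01)² = 0.0016 − 0.00000016, that is 0.0016. The printed term is 0.0491, about 31 times larger.

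**4. The null term depends on the test.**
- Wald, or 90% confidence interval: the same variance, 0.0016, without M.
- Restricted score test: 2q + M − M², where q is the estimate of p10 constrained to p01 = p10 + M. It solves p10/q + p01/(q + M) = 2(1 − p01 − p10)/(1 − 2q − M). Here q = 0.00048 and the null variance is 0.0485, close to the printed 0.0516.

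**5. n at the printed inputs with the correct terms.**
- Wald: (1.6449 + 0.8416)²·0.0016/0.00254 = 3.9, so 4.
- Score: [1.6449·√0.0485 + 0.8416·√0.0016]²/0.00254 = 61.7, so 62.

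Neither is a usable target. At 124 surfaces the expected number of discordant pairs is 124 × 0.0016 = 0.2, and normal approximations fail there.

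**6. Exact power at 124 surfaces.** This enumerates the binomial number of discordant pairs and their split.
- Score test: 99.99%.
- Wald/90% interval: above 99.99%.
- A McNemar-type statistic with nM added to numerator and variance: 99.8%.

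At 149 and 154 surfaces the score and Wald tests both exceed 99.99%.

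**7. Larger discordance (assumed values, M = 5%).**

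| p01 / p10 | Printed n | Score n | Wald n | Printed ÷ score |
|---|---|---|---|---|
| 2% / 2% | 221 | 147 | 99 | 1.50 |
| 3% / 3% | 270 | 188 | 149 | 1.44 |
| 5% / 5% | 369 | 274 | 248 | 1.35 |
| 10% / 10% | 617 | 507 | 495 | 1.22 |
| 6% / 10% | 159 | 131 | 121 | 1.21 |

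Exact score-test power at the printed n is 95% (221), 93% (270), 90.5% (369) and 88% (159, for 6%/10%).

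At the planned 149 surfaces, exact score-test power is about 71% (3%/3%), 57% (5%/5%), 38% (10%/10%) and 86% (6%/10%).

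**The case against.** Five points can be made for the plan.

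- **The error is on the safe side.** This stands. At equal inputs the printed n was larger than the correct one throughout the range examined. A reader might infer that the formula leaves the trial underpowered; the arithmetic shows the opposite at the printed inputs.
- **M is not wrong everywhere.** This stands too. A reader might infer that M must be struck from both square roots. For a restricted score test M properly belongs in the null variance, and the printed value is then about 6% too high (0.0516 against 0.0485). Only the z_beta term is wrong for both tests.
- **The article never prints 124, and attaches 0.8 to 154.** True. The comparison with 80% rests on the inference from 149 − 25. The conclusion does not change at 149 or 154. At a literal 12 surfaces the score test has almost no power, but 12 is not what the formula returns.
- **Near-100% power partly reflects the near-zero discordance.** Correct. Even the score formula's 62 surfaces have exact power of about 96%. With 6%/10% the gap is only about 8 points (88% at 159).
- **The correct n depends on a test the article does not name.** Correct, and this is why the test has to be named first.

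One further reading is tempting: since the corrected n is smaller, the sample could be cut, or the planned number is comfortably large. The figures do not support this. The gain exists only at equal inputs, and at larger discordance 149 surfaces fall short of 80% power.

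**Conclusion.** The point holds as a formula error with a conservative direction. The variance under the alternative is 0.0491 where the plan's own inputs give 0.0016, and the resulting 124 surfaces carry about 99.8–100% power against the 5% margin rather than 80%. With discordant proportions of 2–10% each, the printed n is about 20–50% above the score-test n, and further above the Wald n where discordance is low (221 against 99 at 2%/2%).

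This rests on independent surfaces, one-sided alpha 0.05, M = 5% absolute, and 124 as the formula's output. Several surfaces per child would need a separate allowance. The disagreement between 12, 149 and 154, and the absence of a margin from a plain McNemar test, are separate matters; settling them would not repair the formula. The finding supports restating the power. It supports neither a claim of underpowering caused by the formula nor a smaller trial.

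**What to change.** 1. In the section on statistical treatment of data, name the margin-based test. The simplest choice that fits the planned interval is to declare non-inferiority if the lower limit of the 90% confidence interval for the paired difference (scanner minus radiograph) lies above −5%.
2. In Sample calculation, replace the displayed formula with the one for that test:
   - Wald: n = (z_alpha + z_beta)²·[p01 + p10 − (p10 − p01)²] / (p10 + M − p01)²; or
   - restricted score: n = [z_alpha·√(2q + M − M²) + z_beta·√(p01 + p10 − (p10 − p01)²)]² / (p10 + M − p01)², with q defined as in the working.
3. Restate the power at the planned number of surfaces in both sections, by exact enumeration and over a stated range of discordant proportions, for example 2% to 10% each.
4. Do not lower the sample on the strength of the 0.06% and 0.1% inputs.

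Cost: rewording of two sections and a short recalculation. The correction to the formula asks for no additional children or procedures. Whether the restated power is acceptable at realistic discordance is a decision for the sponsor once the range is shown.

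### The sample size rests on near-zero discordance (0.06% and 0.1%), which is implausible beside the expected moderate kappa, so the stated power of 0.8 is unsupported

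*Protocol article*

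**What the plan says.** The section Sample calculation gives a paired McNemar formula and adapts it: "Similar formulae can be obtained for the one-sided non-inferiority test by substituting" the one-sided critical value and adding the margin M to p10. Its inputs are "where significance level *α* = 0.05, power 1 –β = 0.8" and "non-inferiority margin M = 5%, assumed detection rate *p*_01_ = 0.06%, *p*_10_ = 0.1", the last figure also in per cent. The result is printed as "The minimum sample size required is 12 surfaces". It continues: "Assuming the drop off rate to be 20%, an additional 25 surfaces will be recruited", and concludes that "the total number of surfaces needed for the clinical trial is 149, requiring 80 patients".

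The section Organization and statistical treatment of data then says "A minimum of 154 surfaces will ensure a power of 0.8, with an alpha = 0.05" and, on agreement, "Moderate agreement (Kappa≥0.5) is expected between iTero Element 5D system and radiography". It names McNemar's test for non-inferiority and a 90% confidence interval for the differences, which matches a one-sided 5% level. Neither section gives the proportion of surfaces expected to be positive.

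**The concern.** In a McNemar calculation, p01 and p10 are the probabilities that exactly one of the two methods calls a surface positive. Their sum is the disagreement rate, and that rate drives the variance. The protocol labels them a detection rate and sets the sum at 0.16%, so the scanner and the radiograph would agree on 99.84% of surfaces. The next section expects moderate agreement.

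If disagreement is at the level that moderate kappa usually implies, the paired difference is much noisier than the calculation allowed. The confidence interval could then cross a 5% margin even when the scanner is no worse than radiography. The power of 0.8 is the only justification printed for the number of surfaces and children.

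**Working it through.** **1. Reproduce the plan's figure.** Inputs from Sample calculation: p01 = 0.0006, p10 = 0.001, M = 0.05, z for one-sided 5% = 1.645, z for 80% power = 0.842.

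- Sum with margin: 0.0006 + 0.001 + 0.05 = 0.0516.
- Difference with margin: 0.001 + 0.05 − 0.0006 = 0.0504, squared 0.00254.
- n = [1.645·√0.0516 + 0.842·√(0.0516 − 0.00254)]² / 0.00254 = (0.3736 + 0.1864)² / 0.00254 = 123.5, so 124.
- 124 × 1.2 = 148.8, so 149, an addition of 25.

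The text prints 12 where 124 belongs; 124 is inferred from 149 − 25. The literal percentages therefore reproduce the plan's total.

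**2. How much the discordance contributes.** With p01 = p10 = 0 the same formula gives 121.5. Almost the whole sample size comes from M.

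**3. What 0.16% discordance implies.**

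- Expected discordant surfaces: 149 × 0.0016 = 0.24.
- Chance of none: 0.9984^149 = 0.79.
- With both methods positive on a fraction π of surfaces, kappa = 1 − D/[2π(1−π)], where D is total discordance. For D = 0.0016, kappa is 0.983 at π = 5%, 0.991 at 10%, 0.995 at 20% and 0.997 at 50%.

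**4. Power if kappa is 0.5.** Then D = π(1−π). The positivity values are assumed, because the protocol gives none. Also assumed are equal detection, independent surfaces and the 5% margin at one-sided 5%. With the usual paired-difference variance, power = Φ(0.05·√n/√D − 1.645). At n = 149 and π = 20%: 0.05 × 12.207 / 0.4 = 1.526; 1.526 − 1.645 = −0.119; power 45%.

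| Positivity | D | Power at 149, paired-difference variance | Power at 149, plan's formula | Surfaces for 80%, paired-difference / plan's formula |
|---|---|---|---|---|
| 5% | 4.75% | 88% | 62% | 118 / 240 |
| 10% | 9% | 65% | 49% | 223 / 345 |
| 20% | 16% | 45% | 38% | 396 / 518 |
| 30% | 21% | 38% | 33% | 520 / 641 |
| 50% | 25% | 34% | 30% | 619 / 740 |

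Keeping the plan's 0.04-point difference instead of zero moves the plan's-formula power only slightly (63% at 5% positivity, 50% at 10%). Using 154 surfaces instead of 149 adds about one percentage point. The surface counts are before any loss.

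**5. If 6% and 10% were meant.** The plan's formula gives 1.2813 / 0.0081 = 158.2, so 159. After loss this is 199 (159/0.8), or 191 by the plan's way of adding 20%. By that formula, power is 71% at 124 surfaces and 78% at 149. The paired-difference variance gives 121 surfaces for the same inputs, but only because they assume one method detects 4 points more.

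**The case against.** A reader might infer that the two assumptions cannot both be true. The protocol does not support that. Kappa of 0.5 is written as a floor, so a kappa near 1 satisfies it. Even kappa of exactly 0.5 fits 0.16% discordance at about 0.16% positivity, although 149 surfaces would then hold about 0.24 positives. The word moderate points to values near the floor, so implausible together is the fair description.

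A reader might also infer that a non-inferior scanner would more likely fail than pass. That holds only under conditions:

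- **Positivity.** Surfaces with evident cavities or restorations are excluded, so low positivity cannot be ruled out. At kappa 0.5 with equal detection, the paired-difference power exceeds 50% up to about 15% positivity (53% there) and meets 80% at 5%.
- **Kappa above the floor.** At 10% positivity, kappa 0.7 gives 84%. At kappa 0.8, power is 78%, 68% and 61% at 20%, 30% and 50% positivity.
- **True difference.** Equal detection is an assumption of this check. The plan has p10 above p01 in a 10:6 ratio. Keeping that ratio at kappa of about 0.5 gives about 87% at 20% to 50% positivity. That needs a true scanner advantage of about 4 to 6 points, whereas the printed inputs imply 0.04 points.

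Three further points stand. Adding M to the variance makes the formula conservative (518 against 396 at 20% positivity), so it is not the cause of any shortfall. Other near-zero inputs give nearly the same n (0.0005 and 0.001 give 122.7), so matching 124 does not by itself prove which values were used; it shows that the printed ones suffice. And the inclusion criteria ask for at least two eligible surfaces per child, so the analysed number may exceed 149.

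None of this supplies the missing basis for a guaranteed power of 0.8.

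**Conclusion.** The point holds as an unsupported power claim resting on an implausible input. The printed discordance carries almost no weight in the sample size and sits badly with the agreement the protocol expects. Under the assumptions in step 4, power at 149 surfaces runs from 88% at 5% positivity to 34% at 50%; by the plan's own formula it is below 80% throughout. These figures depend on a positivity rate and a true difference that the protocol does not state, so they are a range and not a prediction that the trial will fail. A misplaced per cent sign does not rescue the figure, because the plan's formula then asks for 159 surfaces before loss.

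**What to change.** In Sample calculation, label p01 and p10 as discordant-cell probabilities. State the positivity rate, kappa and true difference assumed, and derive p01 and p10 from them so that they agree with the kappa given in the analysis section. Recompute the number of surfaces, and correct the printed 12. In the analysis section, replace the assurance of 0.8 with the power reached at the number of surfaces actually planned, shown over the range of positivity and difference considered credible.

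This means rewriting a paragraph and a sentence. The cost is a less favourable stated power over much of that range.

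Two further steps are optional: a variance without M, and scoring every eligible surface in the enrolled children with clustering within child handled in the analysis. The second adds examiner time, since two examiners assess each included surface independently at visual inspection.
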